## Abstract

Cervicogenic headache (CEH) is a secondary headache which affects 1.0–4.6 % of the population. Although the costs are unknown, the health consequences are substantial for the individual; especially considering that they often suffers chronicity. Pharmacological management has no or only minor effect on CEH. Thus, we aim to assess the efficacy of chiropractic spinal manipulative therapy (CSMT) for CEH in a single-blinded placebo-controlled randomized clinical trial (RCT). According to the power calculations, we aim to recruit 120 participants to the RCT. Participants will be randomized into one of three groups; CSMT, placebo (sham manipulation) and control (usual non-manual management). The RCT consists of three stages: 1 month run-in, 3 months intervention and follow-up analyses at the end of intervention and 3, 6 and 12 months. Primary end-point is headache frequency, while headache duration, headache intensity, headache index (frequency × duration × intensity) and medicine consumption are secondary end-points. Primary analysis will assess a change in headache frequency from baseline to the end of intervention and to follow-up, where the groups CSMT and placebo and CSMT and control will be compared. Due to two group-comparisons, the results with p values below 0.025 will be considered statistically significant. For all secondary end-points and analyses, the significance level of 0.05 will be used. The results will be presented with the corresponding p values and 95 % confidence intervals. To our knowledge, this is the first prospective manual therapy three-armed single-blinded placebo-controlled RCT to be conducted for CEH. Current RCTs suggest efficacy in headache frequency, duration and intensity. However a firm conclusion requires clinical single-blinded placebo-controlled RCTs with few methodological shortcomings. The present study design adheres to the recommendations for pharmacological RCTs as far as possible and follows the recommended clinical trial guidelines by the International Headache Society.

*Trial registration* ClinicalTrials.gov identifier: NCT01687881, 2 December 2012

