### Primary and secondary end-points

The primary and secondary end-points are listed in Table 2. The end-points adhere to the recommended IHS clinical trial guidelines (Tfelt-Hansen et al. 2000; Silberstein et al. 2008). We define number of headache days to be primary end-point and expect at least 25 % reduction in average number of days from baseline to the end of intervention, with the same level of reduction maintaining at follow-up. Based on previous reviews on CEH, a 25 % reduction is considered to be a conservative estimate (Chaibi and Russell 2012). A 25 % reduction from baseline to the end of intervention and follow-up is also expected in secondary end-points for headache duration, headache intensity, and headache index, where the index is calculated as mean days with headache (30 days) × mean headache duration (hours per day) × mean intensity (0–10 NRS). A 50 % reduction in medication consumption from baseline to the end of intervention and to follow-up is expected.

**Table 2 Tab2:** Primary and secondary end-points

Primary end-points
1. Number of headache days in active treatment vs. placebo group
2. Number of headache days in active treatment vs. control group
Secondary end-points
3. Headache duration in hours in active treatment vs. placebo group
4. Headache duration in hours in active treatment vs. control group
5. Self-reported VAS in active treatment vs. placebo group
6. Self-reported VAS in active treatment vs. control group
7. Headache index (frequency × duration × intensity) in active treatment vs. placebo group
8. Headache index in active treatment vs. control group
9. Headache medication dosage in active treatment vs. placebo group
10. Headache medication dosage in active treatment vs. control group

The data analysis is based on the run-in period vs. end of intervention. Point 11–40 will be duplicate of point 1–10 above at respectively 3, 6 and 12 months follow-up

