**Fig. 2 Fig2:**
[figure not shown]
Expected participants flow diagram

Change in primary and secondary end-points from baseline to the end of intervention and to follow-up will be compared between active and placebo and active and control group. Null-hypothesis states that there is no significant difference between the groups in average change, while the alternative hypothesis states that a difference of at least 25 % exists.

Due to follow-up period, repeated recordings of primary and secondary end-points will be available, and analyses of trend in primary and secondary end-points will be of main interest. Intra-individual correlations (cluster effect) are likely to be present in data with repeated measurements. Cluster effect will thus be assessed by an intra-class correlation coefficient (ICC) quantifying the proportion of total variation attributable to the intra-individual variations. The trend in end-points will be assessed by a linear regression model for longitudinal data (linear mixed model) to correctly account for possible cluster effect. Linear mixed model handles unbalanced data, enabling all available information from randomized patients to be included, also from drop-outs. Regression models with fixed effects for time component and group allocation as well as the interaction between the two will be estimated. The interaction will quantify possible differences between groups regarding time trend in the end-points and serve as an omnibus test. Random effects for patients will be included to adjust the estimates for intra-individual correlations. Random slopes will be considered. The linear mixed models will be estimated by SAS PROC MIXED procedure. The two pairwise comparisons will be performed by deriving individual time point contrasts within each group with the corresponding p values and 95 % confidence intervals (CI).

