Both per-protocol and intention-to-treat analyses will be conducted if relevant. All analyses will be performed by a statistician, blinded for group allocation and participants. All adverse effects will also be registered and presented. Participants who experience any sort of adverse effects during the trial period will be entitled to call the prime investigator on the project cell phone. The data will be analyzed with SPSS v22 and SAS v9.3. Because of two group-comparisons in a primary end-point, p values below 0.025 will be considered statistically significant. For all secondary end-points and analyses, a significance level of 0.05 will be used. Missing values might appear in incomplete interview questionnaires, incomplete headache diaries, missed intervention sessions and/or due to drop-outs. The pattern of missingness will be assessed and missing values handled adequately.

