### Power calculation

Sample size calculations are based on the results in a recently published group comparison study on topiramate (Silberstein et al. 2004). We hypothesize that the mean difference in reduction of number of days with headache per month between active and the placebo group is 2.5 days. The same difference is assumed between active and the control group. Standard deviation for reduction in each group is assumed to be equal 2.5. Under the assumption of on average 10 headache days per month at baseline in each group and no change in the placebo or control group during the study, 2.5 days reduction corresponds to a reduction by 25 %. As primary analysis includes two group-comparisons, we set a significance level at 0.025. A sample size of 20 patients is required in each group to detect a statistical significant mean difference in reduction of 25 % with 80 % power. To allow for drop-outs, the investigators plan to recruit at least 120 participants.

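### All 32 secondary contrasts are tested at an unadjusted 0.05, with no order, gate or supportive label, although the primary is corrected for the same two comparisons

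*Protocol article*

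**What the plan says.** The threshold for the primary end-point is explained in Data processing: "Because of two group-comparisons in a primary end-point, p values below 0.025 will be considered statistically significant". Power calculation gives the same reason: "As primary analysis includes two group-comparisons, we set a significance level at 0.025". The secondary end-points get a different rule, also in Data processing: "For all secondary end-points and analyses, a significance level of 0.05 will be used". The Abstract repeats it.

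The Abstract names four secondary end-points: "headache duration, headache intensity, headache index (frequency × duration × intensity) and medicine consumption are secondary end-points". Table 2 lists each against placebo and against control (points 3–10), and its note adds: "Point 11–40 will be duplicate of point 1–10 above at respectively 3, 6 and 12 months follow-up".

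Data processing says that changes in both primary and secondary end-points "will be compared between active and placebo and active and control group". It gives a single null and a single alternative hypothesis for both kinds of end-point. The section Primary and secondary end-points attaches an expected reduction of 25 % to duration, intensity and index. For medication it says: "A 50 % reduction in medication consumption from baseline to the end of intervention and to follow-up is expected".

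The model in Data processing includes a group-by-time interaction as an overall test, followed by contrasts at individual time points with p values and 95 % confidence intervals. Nothing says that the contrasts depend on the overall test or on the primary result.

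**The concern.** The article recognises that two group comparisons need a stricter threshold and applies this to headache days. Every secondary end-point has the same two comparisons with the same shared CSMT arm, and is repeated at four time points, yet each contrast is judged at 0.05. For the same pair of arms, a secondary result therefore faces a looser bar than the primary.

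Unadjusted secondary tests do little harm when they are labelled supportive. Here they carry hypotheses and expected effects, and the stated rule calls p < 0.05 significant. Nothing in the article would prevent one of the 32 contrasts, perhaps at a single follow-up visit, from being called significant when both primary comparisons have failed.

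**Working it through.** **1. The plan's own figure.** Inputs from Power calculation: difference 2.5 days, SD 2.5, significance level 0.025, power 80 %. Sidedness is not stated; two-sided is assumed.

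n per group = 2 × (2.241 + 0.842)² × (2.5/2.5)² = 2 × 9.505 = 19.0, rounded up to 20.

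This reproduces the stated 20 per group (power 82.1 % by the normal approximation, 79.3 % by the exact t calculation). One-sided 0.025 would give 16, so the two-sided reading fits, and it is used below. For the primary, 0.025 + 0.025 = 0.05 at one time point. The article gives no corresponding figure for the secondary family.

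**2. Size of the secondary family.** 4 end-points × 2 comparisons × 4 time points (end of intervention, 3, 6 and 12 months) = 32. Cross-check from Table 2: 40 points in all, less 2 × 4 = 8 for headache days, leaves 32.

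**3. No true effects, independent tests at 0.05.**
- Expected false positives: 32 × 0.05 = 1.6. This does not depend on correlation.
- At least one of 32: 1 − 0.95³² = 0.806.
- At least one of the 8 at end of intervention: 1 − 0.95⁸ = 0.337.

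**4. Allowing for correlation.** With equal allocation and equal variances, the two comparisons share the CSMT mean. Their covariance is σ²/n and each variance is 2σ²/n, so their correlation is 0.5. Correlations between end-points and between time points are not in the article and are assumed. Simulated z statistics (100,000 draws per setting, two-sided 0.05, no true effects) give, for the 32 contrasts:

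| Between end-points | Between times | At least one false positive |
|---|---|---|
| 0 | 0 | 78 % |
| 0.3 | 0.3 | 73 % |
| 0.5 | 0.5 | 64 % |
| 0.5 | 0.8 | 52 % |
| 0.7 | 0.7 | 49 % |
| 0.8 | 0.8 | 40 % |
| 0.9 | 0.9 | 28 % |

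The index is built partly from duration and intensity. Letting it correlate 0.7 with both gives 64 % at a time correlation of 0.5, 51 % at 0.8 and 44 % at 0.9.

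The eight end-of-intervention contrasts alone give 32 % with the shared arm only, and 30 %, 27 % and 23 % at end-point correlations of 0.3, 0.5 and 0.7.

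**5. If the interaction test were a gate.** With one gate at 0.05 for each of four end-points and no true effects, the error is at most 1 − 0.95⁴ = 18.5 % if the gates are independent. The Bonferroni bound is 4 × 0.05 = 20 %.

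**The case against.** The confirmatory claim is clear: one primary end-point, headache days, with 0.025 for each of its two comparisons. Leaving declared secondary end-points at a nominal 0.05 is common, is stated openly twice, and does not touch the primary rule. Confidence intervals are reported throughout. A test order or a supportive label is often left to an analysis plan, which is not shown. The interaction test may also have been meant to screen the contrasts.

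Much of this stands. The primary error rate is not affected, no stated figure is wrong, and the article nowhere says that a lone secondary result would be presented as proof of efficacy. But the point concerns a rule that the article does state. An analysis plan that added a hierarchy or withdrew significance claims would depart from it. The article leaves open whether the interaction test gates anything, and step 5 shows that gating would not bring the error to 0.05.

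A reader might infer that a false significant secondary result is more likely than not. The documents do not support that without conditions. It needs all 32 null hypotheses to be true and correlations that are low to moderate. Higher correlations are plausible, because the same patients are measured repeatedly, the arms are shared and the index overlaps with its components. At 0.7/0.7 the figure is already just under one half, and for the eight end-of-intervention tests it never reaches one half.

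**Conclusion.** The point holds as a limit on what the secondary p values can support. A stated rule allows 32 significance claims with no control across them, while the same two comparisons are corrected for the primary.

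With no true effects, 1.6 false positives are expected. The chance of at least one is 81 % under independence, about 49–73 % at assumed correlations of 0.3–0.7, and about 28 % at 0.9, which is still more than five times 0.05. These figures rest on two-sided tests, all secondary nulls being true and, for the correlated settings, a shared-arm correlation of 0.5. The end-point and time correlations are assumptions.

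The point does not extend to headache days at 3, 6 and 12 months. The Abstract puts follow-up within the primary analysis, and the opening of Methods and design expects the reduction to persist there.

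**What to change.** Replace the 0.05 sentence in the Abstract and in Data processing with:

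*Secondary end-points are supportive; they are reported as estimates with 95 % confidence intervals and nominal p values, without confirmatory claims of statistical significance.*

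The present sentence also covers secondary analyses, so the authors should say whether these take the same label.

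If a confirmatory secondary claim is wanted, test the secondaries at the end of intervention in a fixed, stated order. Do so only for a comparison whose primary test has succeeded, at that comparison's 0.025, stopping at the first non-significant result. If each comparison's primary claim is itself held to 0.025, the two sequences together stay within 0.025 + 0.025 = 0.05. Bonferroni over all 32 would instead need 0.05/32 = 0.0016 per test.

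Limit the change to secondary end-points, and leave headache days at follow-up to the definition of the primary analysis.

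The cost is a change of wording in two places, with no new data or patients. The downside is that an isolated secondary p < 0.05 can no longer be claimed as significant.

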### Power calculation

Sample size calculations are based on the results in a recently published group comparison study on topiramate (Silberstein et al. 2004). We hypothesize that the mean difference in reduction of number of days with headache per month between active and the placebo group is 2.5 days. The same difference is assumed between active and the control group. Standard deviation for reduction in each group is assumed to be equal 2.5. Under the assumption of on average 10 headache days per month at baseline in each group and no change in the placebo or control group during the study, 2.5 days reduction corresponds to a reduction by 25 %. As primary analysis includes two group-comparisons, we set a significance level at 0.025. A sample size of 20 patients is required in each group to detect a statistical significant mean difference in reduction of 25 % with 80 % power. To allow for drop-outs, the investigators plan to recruit at least 120 participants.

### Ethics

The study has been approved by the Norwegian Regional Committee for Medical Research Ethics (REK) (2010/1639/REK) and the Norwegian Social Science Data Services (11–77). The declaration of Helsinki is otherwise followed. All data will be anonymised while participants must give oral and written informed consent, including consent to publish all obtained data. Insurance is provided through “The Norwegian System of Compensation to Patients” (NPE) which is an independent national body, set up to process compensation claims from patients who have suffered an injury as a result of treatment under the Norwegian health service. A stopping rule is defined for withdrawing participants from this study in accordance with recommendations in the CONSORT extension for Better Reporting of Harms (Ioannidis et al. 2004). If a participant reports to their chiropractor or research staff a severe adverse event, he or she will be withdrawn from the study and referred to their General Practitioner or hospital emergency department depending on the nature of the event. Data will be stored in a locked cabinet at the Research Centre, Akershus University Hospital, Norway, for 5 years.

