### Patient population

Participants will be recruited in the period September to October 2012 through Akershus University Hospital and Innlandet Hospital Trust, Norway. Participants will receive posted information about the project followed by a short telephone interview.

Eligible participants are between 18 and 70 years of age and have at least one headache attack per month. Participants are diagnosed according to at least three major criteria not including occipital nerve blockage from the diagnostic criteria of the Cervicogenic Headache International Study Group (Sjaastad et al. 1998; Knackstedt et al. 2010). All participants are diagnosed by a neurologist.

Exclusion criteria are contraindication to SMT, spinal radiculopathy, pregnancy, depression and CSMT within the previous 12 months. Participants whom during the RCT receive any manual interventions by physiotherapists, chiropractors, osteopaths or other health professionals to treat musculoskeletal pain and disability, including massage therapy, joint mobilization and manipulation (French et al. 2011), changed their prophylactic headache medicine or pregnancy will be withdrawn from the study at that time and be regarded as drop-outs.

In response to initial contact, participants fulfilling the inclusion criteria will be invited to further assessment by the chiropractic investigator. The assessment includes an interview and a physical examination with special emphasis on the whole spinal column. Oral and written information about the project will be provided in advance and written consent will be obtained from all accepted participants during the interview by the clinical investigator. In accordance with good clinical practice, all patients will be informed about the harms and benefits as well as possible adverse reactions of the intervention primarily including local tenderness and tiredness on the treatment day. No serious adverse events have been reported for the chiropractic Gonstead method (Cassidy et al. 2008; Tuchin 2012). Participants randomized into active or placebo interventions, will undergo a full spine radiographic examination and be scheduled for 12 intervention sessions. The control group will not be exposed to this assessment.

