### Follow-up

Follow-up analysis will be conducted on the end-points measured after the end of intervention and 3, 6 and 12 months follow-up. During this period all participants will continue to fill in a diagnostic headache diary and return it on a monthly basis. In the case of unreturned diary or missing values in the diary, the participants will be contacted immediately upon detection to minimize recall bias. Participants will be contacted by phone to secure compliance.

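### The severe adverse event rule takes the participant out of the study, not just out of the sessions, so later diaries are lost for a harm-related reason

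*Protocol article*

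**What the plan says.** The protocol article, Ethics, introduces the provision with "A stopping rule is defined for withdrawing participants from this study". It then applies the rule to anyone who reports "a severe adverse event, he or she will be withdrawn from the study and referred to their General Practitioner or hospital emergency department". Both sentences speak of leaving the study. Neither mentions sessions or treatment.

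Four other places bear on how this is to be read:

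- **Patient population.** Participants who receive manual treatment elsewhere, change prophylactic medicine or become pregnant "will be withdrawn from the study at that time and be regarded as drop-outs". The Discussion (Methodological considerations) repeats the drop-out status for manual treatment received elsewhere.
- **Follow-up.** "During this period all participants will continue to fill in a diagnostic headache diary and return it on a monthly basis", and "Participants will be contacted by phone to secure compliance".
- **Data processing, adverse effects.** "All adverse effects will also be registered and presented".
- **Data processing, analysis.** The linear mixed model is chosen as "enabling all available information from randomized patients to be included, also from drop-outs".

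**The concern.** Stopping treatment and ending observation are different decisions. After a severe adverse event there is good reason to stop manipulation or sham and to send the person for care. There is no matching reason to stop asking for a headache diary or to stop phoning. A rule that does both makes outcome data missing because of a harm, and harms may not be equally common under manipulation, sham and no contact.

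The Discussion counts safety data among the things a randomised trial is best placed to deliver, and the Background says that no randomised trial has yet applied the Gonstead method. The few people with a severe event are the ones whose later course would be most informative, and they are the ones this rule would lose sight of.

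**Working it through.** **1. What the rule means.** Set the texts side by side.

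- Ethics: the trigger is a severe adverse event; the consequence is withdrawal from the study plus referral. Withdrawal is automatic.
- Patient population and Discussion: the triggers are different, but the phrase is the same, and there it goes with drop-out status from that time.
- Follow-up: diaries and calls are planned for all participants. Nothing says that this includes people already withdrawn.
- Nowhere does the article use the phrase to mean that sessions stop while follow-up goes on.

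Study exit is therefore the plain reading. It is an inference, because the Ethics section does not state that diaries end.

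**2. What is kept and what is lost on that reading.**

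- Kept: registration of the event itself, and all diary data up to withdrawal, which the mixed model uses.
- Lost: diaries after the event, and the phone contacts through which the course of the event could have been learned. The mixed model cannot use diaries that were never requested.

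**3. The protocol's own sample size, as a check on inputs.** From Power calculation: difference 2.5 days, SD 2.5, significance level 0.025, power 80 %. Taking the test as two-sided, with the normal approximation:

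n per group = 2 × (z(0.9875) + z(0.80))² × (SD/difference)² = 2 × (2.241 + 0.842)² × 1² = 19.01, rounded up to 20.

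This reproduces the stated 20 per group.

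**4. How many people.** Recruitment target 120, so 120 / 3 = 40 per arm. The article gives no rate of severe events. Assume 0 to 2 per arm: 2 / 40 = 5 %, and 3 × 2 = 6 people at most. Under Patient population the article says "No serious adverse events have been reported for the chiropractic Gonstead method" (serious is not the same term as severe) and expects mainly local tenderness and tiredness, so zero is plausible.

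**5. Effect on power.** Power ≈ Φ(√(n/2) × difference/SD − 2.241), with difference/SD = 1. The t-test column uses the noncentral t distribution on the same inputs.

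| n per arm | √(n/2) | Normal approximation | t-test |
|---|---|---|---|
| 40 | 4.472 | 98.7 % | 98.5 % |
| 39 | 4.416 | 98.5 % | 98.2 % |
| 38 | 4.359 | 98.3 % | 97.9 % |

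The largest fall is 0.4 percentage points (normal) or 0.6 (t-test). It takes only these losses into account and treats the affected people as contributing nothing, although their earlier data would in fact be used.

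**6. Volume of follow-up at stake.** Months after run-in: 3 + 12 = 15. At most 6 × 15 = 90 monthly diaries, out of 120 × 15 = 1,800 if everyone completed. The upper end requires every event to occur at the very start of the intervention.

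**The case against.** The strongest reply is that the harm is inferred. The Ethics section never says that contact ends. The Patient population and Discussion sentences add drop-out status in separate words, which would be unnecessary if withdrawal alone already meant it, and their triggers differ. That stands as a limit on certainty. It does not remove the point, because the article states an automatic rule whose object is the study, and no section keeps a withdrawn participant under observation.

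A reader might go further in three ways that the documents do not support:

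- **That the rule ends a programme of safety monitoring.** Run-in describes the diary as covering the primary and secondary end-points, and the phone contact is there to secure compliance. No scheduled safety visits are described. Adverse effects are registered, and participants may call the investigator; nothing says that either lapses on withdrawal. The loss is mainly headache-diary data, together with the chance to learn how the event resolved.
- **That the silence on controls and on the follow-up period is an error.** A condensed article commonly leaves such scope to the full protocol, which is not shown.
- **That the primary result is at risk.** The figures above show that it is not, in terms of power. The size of any bias cannot be computed without an event rate, but with so few people it is unlikely to be material.

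It is also fair to say that an automatic stop is a safeguard. One chiropractor, who is not blinded, gives all sessions, so making the session stop a matter of clinical discretion would weaken protection. The fix should keep that part mandatory.

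**Conclusion.** The point holds as a low-priority improvement. As written, and read consistently with the rest of the article, the rule ends later diaries and contacts for a reason related to harm. The event is still registered, and earlier data are still analysed. With an assumed 0 to 2 affected people per arm (0 to 6 in all), the effect on power is negligible and the primary conclusion is unlikely to change. The cost of leaving the rule alone is a small amount of harm-related missing follow-up, and not knowing the later course of what may be the trial's most important safety cases.

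Confidence is medium. It rests on reading withdrawal from the study as study exit, and on an event rate that the document does not supply. If the full protocol already separates stopping treatment from leaving the study, only the article's wording is at fault.

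**What to change.** Reword the Ethics rule so that it says three things:

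1. A severe adverse event always stops any further study sessions and triggers referral to the general practitioner or emergency department.
2. The participant stays in the study: the monthly diaries and phone contact set out under Follow-up continue to 12 months unless the participant withdraws consent.
3. The outcome of the event is recorded at those contacts.

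The cost is a protocol amendment with matching consent wording, and possibly renewed consent if participants are already enrolled. There would be at most 15 extra monthly diaries per affected person, so 0 to 90 in total under the assumption above, plus the related calls. Continued contact also asks a little more of people who have just been unwell, which is why it must depend on their consent.
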